# Epidural injection of dexamethasone palmitate vs. betamethasone for lumbar radiculopathy, study protocol for a multi-center non-inferiority randomized double-blind controlled trial

**DOI:** 10.3389/fphar.2026.1801501

**Published:** 2026-05-18

**Keywords:** betamethasone (BTM), dexamethasone palmitate (PubChem CID:63,044), epidural steroid injections, lumbar disc hemiation, lumbar radiculopathy

## Abstract

**Introduction:**

Lumbar disc herniation is commonly treated with epidural steroid injections to relieve radicular pain. Dexamethasone palmitate, a newer lipophilic formulation, is theoretically safer and provides longer-lasting effects compared to traditional corticosteroids like betamethasone. However, direct clinical evidence comparing their efficacy and safety is still limited.

**Methods:**

This multicenter, randomized, double-blind, non-inferiority trial will enroll 228 patients with confirmed lumbar disc herniation and radicular pain. Participants will be randomly assigned (1:1) to receive an image-guided epidural injection of either DEP or compound betamethasone via interlaminar or transforaminal approach. Follow-up assessments will occur at 1 day, 1 week, 2 weeks, 4 weeks, 8 weeks, and 12 weeks post-injection. The primary outcome is leg pain intensity at 4 weeks, measured by the numeric rating scale (NRS). Secondary outcomes include NRS at other time points, functional disability (ODI and RMDQ), mental health (GAD-7 and PHQ-9), morning serum cortisol, patient satisfaction, and adverse events. A second injection may be administered at 4 weeks based on clinical response.

**Expected outcomes:**

This study will provide the first high-quality evidence on the efficacy and safety of DEP compared with standard particulate corticosteroids for lumbar radiculopathy. Findings are expected to inform clinical decision-making and optimize steroid selection for epidural therapy.

**Clinical Trial registration:**

[https://www.chictr.org.cn], identifier [ChiCTR2400093970].

## Introduction

Lumbar disc herniation is a common cause of radicular pain and disability in adults, resulting from nerve root compression by displaced disc material (Ropper and Zafonte, 2015; Deyo and Mirza, 2016). Epidural steroid injections (ESIs) are widely used and recommended by the North American Spine Society (NASS) guidelines as a cost-effective option that provides significant pain relief in patients with lumbar radiculopathy (McLain et al., 2005; Liu et al., 2023; Kreiner et al., 2014).

Steroids used in ESIs are categorized as particulate and non-particulate types, and differ in their pharmacokinetics, duration of action, and potential side effect profiles. Particulate steroids, such as triamcinolone and compounded betamethasone preparations, have a larger molecular size and remain at the injection site longer due to their delayed absorption (Benzon et al., 2007), a property that theoretically allows for a prolonged anti-inflammatory effect, and may result in more sustained pain relief (Cole and Schumacher, 2005). However, recent case reports have documented instances of paraplegia in patients following lumbosacral nerve root blocks that utilized the particulate steroids betamethasone or methylprednisolone acetate (Aprill and Melfi, 2004; Houten and Errico, 2002). The use of particulate corticosteroids for epidural injections has also been cautioned against by the FDA in 2011 and 2014, stating that “injections into the epidural space may result in rare but serious adverse events, including loss of vision, stroke, paralysis, and death.” Although particulate steroids are associated with rare but serious complications, including spinal cord infarction, they continue to be used in clinical practice, particularly for interlaminar epidural injections or when a longer-lasting anti-inflammatory effect is clinically desirable.

Compared to particulate steroids, non-particulate types (e.g., dexamethasone) are regarded as a safer option for injection into high-risk areas, such as the epidural space and around blood vessels, as they are unable to induce ischemic events due to their small crystalline structure.

Previous studies comparing particulate and non-particulate steroids have suggested that particulate formulations may provide superior analgesic effects and greater short-term improvement in pain outcomes (Bensler et al., 2017).

Dexamethasone palmitate (DEP) a lipophilic prodrug of dexamethasone, has been utilized in clinical practice for the treatment of various conditions, including rheumatoid arthritis and post-transplant hemophagocytic lymph histiocytosis (Lorscheider et al., 2019; Ono et al., 2023). However, no published studies have yet evaluated its efficacy in epidural injection for lumbar disc herniation. Previous studies have suggested that particulate corticosteroids may provide superior and more sustained analgesic effects compared with non-particulate formulations in epidural steroid injection therapy. In this context, it remains unclear whether dexamethasone palmitate, as a novel corticosteroid formulation with distinct pharmacokinetic properties, can achieve comparable clinical efficacy to particulate steroids in the treatment of lumbar radiculopathy. Therefore, a non-inferiority design will be adopted to determine whether dexamethasone palmitate can provide clinically acceptable and comparable outcomes to a commonly used particulate corticosteroid regimen, while potentially offering additional pharmacological or safety advantages.

## Methods and analysis

### Study design

This is a two-arm multi-center, non-inferiority, randomized double-blind controlled trial. Patients with clinically confirmed lumbar disk herniation and radicular pain will be randomly assigned to one of two treatment arms: image guided epidural injection of DEP or combined betamethasone through an interlaminar or transforaminal approach. Follow up will be conducted at 1 day, 1 week, 2 weeks, 4 weeks, 8 weeks, and 12 weeks post-treatment. Pain intensity will be evaluated at all follow up time points, functional outcomes and mental health will be evaluated at 4 weeks, 8 weeks, and 12 weeks follow-up time points. Safety outcomes, including side effects and adverse events will be assessed at 1 day and 4 weeks after treatment. For patients with a pre-existing diagnosis of diabetes, fasting blood glucose levels will be monitored daily for seven consecutive days postoperatively to evaluate the impact of steroids on glycemic control. A repeat injection will be administered based on the patient’s response at 4 weeks of follow-up.

Approval for this study was obtained from the Research Ethics Committee of all the center (approval reference number: 2024-457, 2025-251001, 2024K095, KY-2024-003-02, 2025-06, 2024-41, 2025-002). The trial was registered in the Chinese Clinical Trial Registry (Trial number: ChiCTR2400093970, https://www.chictr.org.cn, Chinese Clinical Trial Registry, 2024-12-15) and the trial protocol followed the ‘Standard Protocol Items: Recommendations (SPIRIT) guideline (Schulz et al., 2010). Patient consent was obtained after enrollment in accordance with the Declaration of Helsinki.

### Study setting

This study will be conducted across seven medical institutions located in Jiangsu Province, China. The participating centers include pain management or orthopedic surgery department in each hospital that have expertise in managing lumbar disk herniation. All have the capacity to conduct clinical trials with appropriate infrastructure and resources, including advanced imaging and pain management facilities, allowing for precise diagnosis and effective treatment delivery (Figure 1).

**FIGURE 1 F1:**
[figure not shown]
Participant flow chart.

### Participant eligibility and trial recruitment

Participants will be recruited primarily from outpatient clinics across the seven participating medical institutions and screened for eligibility based on the inclusion and exclusion criteria outlined below:

### Inclusion criteria

Age ≥18 years.Unilateral buttock or lower limb radicular pain, with or without low back pain.Leg or buttock pain greater than low back pain, with a Numerical Rating Scale (NRS) score ≥4.Magnetic Resonance Imaging (MRI) or Computed Tomography (CT) of the lumbar spine within the past 6 months, confirming the presence of one level lumbar disc herniation with nerve root compression, with clinical symptoms and signs consistent with imaging findings.

### Exclusion criteria

Individuals with known allergies to the study medication.A history of psychiatric disorders.Inability to comprehend the study details, participate in scale assessments, or comply with follow-up visits.Presence of comorbid conditions that could affect the assessment of treatment efficacy, specifically conditions that could cause leg pain (e.g., Parkinson’s disease, diabetic peripheral neuropathy, lower limb thrombosis).Severe cardiovascular diseases that impair daily activities or affect functional assessment scores.Unstable spondylolisthesis (vertebral displacement >3 mm or endplate angle change >15° on dynamic lumbar spine radiographs), or Grade 3 and above spondylolisthesis with instability.Severe osteoporosis with vertebral compression fractures in the segment intended for injection.Malignant tumors with spinal metastasis.Pregnant or breastfeeding women, women planning pregnancy soon, or women whose partners are planning pregnancy.Other contraindications to injection treatments, such as current infection at the puncture site, severe coagulopathy and resulting complications (e.g., gingival bleeding)Recent (within 3 months) history of spinal intrathecal injections.Upcoming surgical plans within the next 3 months.Platelet count below 50 × 10^9^/L or concurrent use of anticoagulant or antiplatelet medications.Presence of the following conditions: posterior subcapsular cataract, glaucoma, herpes simplex keratitis, poorly controlled diabetes (fasting blood glucose ≥7 mmol/L), acute myocardial infarction, peptic ulcer, tuberculosis, infections without effective antibiotic treatment, systemic fungal infections, electrolyte imbalances, recent abdominal surgeries, or thrombosis.

### Study sample size

Assuming there is no difference in the mean NRS score between groups at 4 weeks after treatment, with a standard deviation of 2.2, a two-sided α of 0.05 (equivalent to a one-sided α of 0.025), and a power (1–β) of 0.90, and setting a non-inferiority margin of 1 (less than the minimal clinically important difference of 1.5), a 1:1 allocation ratio between the experimental and control groups was used. Based on PASS software calculations, 102 participants per group were required. After accounting for an estimated 10% loss to follow-up and refusal rate, the final required sample size was determined to be 114 participants per group (Feeley et al., 2017).

A non-inferiority margin of one point on the NRS was selected based on the established minimal clinically important difference (MCID) for radicular pain. This margin was chosen to balance statistical rigor with clinical relevance, allowing detection of whether dexamethasone palmitate maintains acceptable analgesic efficacy compared with standard corticosteroid therapy. From a clinical perspective, demonstrating non-inferiority would support the use of dexamethasone palmitate as a viable alternative treatment option, particularly if it offers additional pharmacological advantages such as prolonged tissue retention or improved safety characteristics.

### Randomization and blinding

Randomization will be performed using a computer-generated random sequence with a 1:1 allocation ratio. Block randomization stratified by study center, duration of symptoms (disease course), and Pfirrmann scale will be applied to ensure balanced distribution of key prognostic factors across treatment groups. The random sequence will be generated by an independent statistician who is not involved in patient recruitment, treatment administration, or outcome assessment.

Allocation concealment will be ensured using a centralized, password-protected randomization system. After enrollment, patients will be assigned to treatment groups by a designated research coordinator at each center, who will not participate in outcome assessment or data analysis.

This study adopts a double-blind design. Participants, treating physicians, outcome assessors and statistician will remain blinded to group allocation.

A dedicated research staff member at each center is responsible for preparing the study medication according to the randomization assignment. The allocated drug is drawn into identical, pre-labelled syringes that are indistinguishable in appearance. After preparation, each syringe is completely covered with an opaque protective sheath to prevent visualization of the solution characteristics.

To further maintain blinding during administration, an opaque injection needle is used so that the appearance of the injectate cannot be observed at any point during the procedure. The syringe and needle remain connected throughout the injection process and are withdrawn as a single unit without disconnection. Immediately after injection, all used materials are handed over to designated unblinded personnel for disposal.

Blinding will be maintained throughout the entire follow-up period. In case of a serious adverse event requiring emergency unblinding, the allocation code may be disclosed by the independent coordinator after appropriate authorization, and all unblinding events will be documented.

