### Measurement of clinical outcomes

Baseline demographic characteristics, including gender, age, education level, occupation, smoking history, allergy history, family medical history, history of diabetes, and current use of analgesics, will be assessed, in addition to patient measurements such as height, weight, the level of lumbar disc herniation, and the severity of nerve compression measured by Pfirmann grading system base on lumbar MRI (Grade I: Herniated disc in contact with the nerve root without displacement; Grade II: Herniated disc in contact with the nerve root, no nerve root displacement; Grade III: Herniated disc in contact with the nerve root, causing posterior displacement of the nerve root; Grade IV: Herniated disc in contact with the nerve root, compressing it against the posterior wall of the spinal canal) (Majeed et al., 2016). Laboratory parameters, including fasting blood glucose and morning serum cortisol levels will also be measured. Pain intensity will be evaluated using the NRS for both low back pain and leg pain. The Oswestry Disability Index (ODI) and Roland-Morris Disability Questionnaire (RMDQ) will be used to assess functional disability. Generalized Anxiety Disorder 7 (GAD-7) and Patient Health Questionnaire 9 (PHQ-9) were used to assess anxiety and depression.

Follow-up assessments will be conducted at post-injection day 1, week 1, week 2, week 4, week 8, and week 12 (Table 1).

**TABLE 1 T1:** Schedule of enrolment, interventions, and assessments.

Timepoint	Enrolment	Baseline	Allocation	Follow up					
	​	​	0	*Day1*	*Week* *1*	*Week* *2*	*Week* *4*	*Week* *8*	*Week* *12*
Enrolment									
Eligibility screen	X	​	​	​	​	​	​	​	​
Informed consent	X	​	​	​	​	​	​	​	​
Allocation	​	​	X	​	​	​	​	​	​
Interventions									
Dexamethasoe palmitate	​	​	X	​	​	​	​	​	​
Combined betamethasone	​	​	X	​	​	​	​	​	​
Assessmens									
*Pain intensity (NRS score)*	​	X	​	X	X	X	X	X	X
*ODI score*	​	X	​	​	​	​	X	X	X
*RMDQ score*	​	X	​	​	​	​	X	X	X
*PHQ-9*	​	X	​	​	​	​	X	X	X
*GAD-7*	​	X	​	​	​	​	X	X	X
*Serum cortisol* *Levels blood glucose*	​	X	​	​	​	​	X	​	​
*Satisfaction*	​	​	​	​	​	​	X	​	​
*Adverse event*	​	​	​	X	X	X	X	X	X

The primary outcome of this study is leg pain measured by NRS score which is measured on a scale of 0–10, with 0 indicating “no pain” and 10 indicating “the worst pain imaginable” at 4 weeks after procedure.

The secondary outcomes are:

Pain: NRS scores at 1 week, 2 weeks, 8 weeks, and 12 weeks post-injection.

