### Primary outcome analysis

The primary outcome (NRS score at 4 weeks) will be analyzed using a linear mixed-effects model, including treatment group, time, and their interaction as fixed effects, with study center as a random effect, baseline NRS score will be adjusted as a covariate.

Non-inferiority will be assessed based on the between-group difference in mean NRS score at 4 weeks post-treatment, with a pre-specified non-inferiority margin of one point. Non-inferiority will be concluded if the upper bound of the two-sided 95% confidence interval for the between-group difference does not exceed the non-inferiority margin. Both intention-to-treat (ITT) and per-protocol (PP) analyses will be performed to ensure robustness of the results.

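### The primary model omits two of the three stratification factors, and Pfirrmann grades I and II, which feed one of those factors, share a single definition

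*Protocol article*

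**What the plan says.** Under Randomization and blinding, the protocol article says "Block randomization stratified by study center, duration of symptoms (disease course), and Pfirrmann scale will be applied", and gives the purpose as "to ensure balanced distribution of key prognostic factors across treatment groups".

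Under Primary outcome analysis, the model contains "treatment group, time, and their interaction as fixed effects, with study center as a random effect", and "baseline NRS score will be adjusted as a covariate". Neither symptom duration nor Pfirrmann grade is among the terms. The terms listed under Secondary outcome analysis do not include them either. Pfirrmann grade returns only under Subgroup analysis; symptom duration is named in no analysis.

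Under Measurement of clinical outcomes, nerve compression is "measured by Pfirmann grading system base on lumbar MRI". Grade I is described as a herniated disc "in contact with the nerve root without displacement; Grade II: Herniated disc in contact with the nerve root, no nerve root displacement". Grades III and IV are described differently from these and from each other.

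The Inclusion criteria accept "Resonance Imaging (MRI) or Computed Tomography (CT) of the lumbar spine within the past 6 months".

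**The concern.** The design and the analysis do not match. When randomisation balances a prognostic factor, the treatment difference varies less from trial to trial than a model without that factor assumes. The standard error is then overstated and the interval for the non-inferiority test is wider than it needs to be. At stake is some precision in the primary test that the stratification has already provided.

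The second matter concerns one of the factors itself. A site must enter a Pfirrmann level before allocation, and the same grade defines a prespecified subgroup. As worded, two of the four levels describe the same finding, and the article does not say how a patient who qualified on CT alone is graded.

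**Working it through.** **Inputs.** From Study sample size: SD 2.2, margin 1 NRS point, true difference 0, one-sided α 0.025, power 0.90, 10% loss. From Study setting: 7 centres. Total 228 patients. Not in the documents, and therefore assumed: R², the share of residual week-4 variance (beyond centre and baseline NRS) explained by symptom duration and Pfirrmann grade, taken as 0.05 to 0.10. As a simplification, 2.2 is used as the residual SD of the model without the two factors.

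**The plan's own figure.** n per arm = 2 × 2.2² × (1.960 + 1.282)² / 1² = 101.7, so 102. Allowing for loss, 102 / 0.90 = 113.3, so 114. Both figures reproduce. No stratification factor enters this formula, so changing the model does not change the planned size.

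**Effect of omission if the two factors are fully balanced.** The model without them uses SE = 2.2 × √(2/102) = 0.308. The true standard deviation of the difference is 0.308 × √(1 − R²).

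- Excess width of interval = 1/√(1 − R²) − 1
- One-sided error at the margin = Φ(−1.96/√(1 − R²))
- Power, factors omitted = Φ((1/0.308 − 1.96)/√(1 − R²))
- Power, factors included = Φ(1/(0.308 × √(1 − R²)) − 1.96)

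| Assumed R² | Excess width | One-sided error | Power, omitted | Power, included |
|---|---|---|---|---|
| 0 | 0 | 2.5% | 90.1% | 90.1% |
| 0.05 | 2.6% | 2.2% | 90.7% | 91.5% |
| 0.10 | 5.4% | 1.9% | 91.2% | 92.8% |

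The loss from omission is 91.5 − 90.7 = 0.8 points at R² = 0.05 and 92.8 − 91.2 = 1.6 points at R² = 0.10.

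**How far balance can be relied on.** The article gives no number of duration classes. If there are two, and all four grades are separate levels, there are 7 × 2 × 4 = 56 strata and 228/56 = 4.1 patients per stratum. Many blocks would stay incomplete. A simulation with these strata, 228 randomised, 204 analysed, assumed block sizes of 4 or 6 and a t-test without the two factors gave a one-sided error of about 2.3% at R² = 0.05 and 2.1-2.2% at R² = 0.10. The direction is the same and the effect is smaller than in the table.

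**The grades, side by side.** Grade I: contact, no displacement. Grade II: contact, no displacement. Grade III: contact with posterior displacement. Grade IV: contact with compression against the canal wall. I and II are indistinguishable as written; III and IV are distinct.

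**Imaging.** The Inclusion criteria admit patients on MRI or CT. Measurement of clinical outcomes and Subgroup analysis base the grade on MRI. Intervention description refers to MRI for the injection level, but to MRI or CT for choosing the nerve root in the transforaminal approach. Table 1 schedules no study MRI. A patient with CT alone is therefore eligible but has no stated route to a grade.

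**The case against.** The strongest reply is that the omission is harmless in the direction that matters. The error stays below 2.5%, power without the two factors is still at or above the planned 90%, and R² is not in the documents. All of this stands. A reader might infer that leaving out stratification factors biases the comparison or makes a false claim of non-inferiority more likely. The calculation shows the opposite: the test becomes slightly conservative. The full-balance figures are also an upper limit, as the simulation shows.

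It could be said that covariates are left to an analysis plan that is not shown. That would hold if the article were silent, but it lists the model's terms and its covariate, and the list does not match its own randomisation.

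On the grades, the repeated description may be a slip in condensing a published scale, and because the grade is set before allocation, misgrading would not bias the treatment comparison. Both points are fair. A reader might also conclude that the Pfirrmann factor cannot be assigned at all. The text does not support that: the difficulty is confined to I versus II and to any patient without an MRI. The number of CT-only patients is unknown and may be zero, since the MRI wording elsewhere may mean that everyone has one. The stratum count likewise rests on an assumed number of duration classes.

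**Conclusion.** The point holds as a modest improvement in efficiency and a correction of wording. As listed, the primary model leaves out two factors that the trial randomises by and calls prognostic. Under an assumed R² of 5-10% and good balance, this costs about 1-2 points of power and puts the one-sided error at about 2.2-1.9% instead of 2.5%. With strata of about four patients the effect is smaller. There is no bias, no inflated error and no wrong sample size.

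The identical wording of grades I and II is a plain textual defect and does not depend on any assumption. The MRI and CT passages are an inconsistency to reconcile; how many patients it affects cannot be judged from the article.

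**What to change.** 1. In the primary and secondary mixed models, add symptom-duration stratum and Pfirrmann stratum as fixed effects, using the levels as randomised, and state the duration classes used.
2. Give grades I and II distinct definitions, or merge these two into one class for the model and the subgroup analysis. Grades III and IV do not overlap, so this defect gives no reason to merge them.
3. Reconcile the MRI-or-CT entry criterion with the MRI-based grade, so that every randomised patient has a defined Pfirrmann stratum. The documents do not support reading this grade from CT, so the authors need to state which rule applies.

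The first two items need only wording and do not alter the planned 102 (114 after loss) per group. The third also needs only wording if every patient already has an MRI. If enrolment has begun, items 1 and 2 can still be made in the analysis plan before unblinding.
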